#### Analysis of the secondary outcomes

The effect of VR immersion on the CPSS, VAS, and MFI-20 scores will be compared using one-way analysis of variance for the 2 × 2 crossover design. Spearman’s rank correlation test will be used to analyze the association between work hours and scores on the scales. The age, BMI, HR, MBP, and the level of satisfaction between groups will be analyzed by the Student *t* test or the Wilcoxon rank-sum test. The gender, incidence of arrhythmia, chest distress, headache, and heart palpitations between groups will be analyzed by the Pearson *χ*^2^ test or Fisher’s exact test.

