## Methods/design

### Study design

The virtual reality immersion in the night-shift anesthesiologist trial is a randomized controlled, single-center clinical trial using a crossover design with a washout of 1 week. Anesthesiologists will be randomized in a 1:1 allocation to a sequence of either immersion relaxation using VR in the first period, followed by no immersion VR in the second treatment period, or no immersion VR in the first period, followed by immersion relaxation using VR in the second period. Anesthesiologists undergoing VR intervention will undergo immersion relaxation via VR twice during the night shift: the first session will occur at 23:30, and the second session will occur at 07:30 the next day. The anesthesiologists will be able to choose VR content and enjoy themselves for 20 min. Anesthesiologists in the control group will not watch VR videos during the night shift. The design of the study is presented in Fig. 1.

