### Setting

The study will be conducted in the Third Affiliated Hospital of Sun Yat-sen University, a large comprehensive hospital in Guangzhou, China. The hospital is a tertiary medical facility that serves as a teaching hospital for Sun Yat-sen University, including 65 anesthesiologists in the Department of Anesthesiology, and the age of the front-line clinicians is 25 to 45. Besides, each anesthesiologist only undergoes one night shift each arm and works from 17:30 to 8:00 of the next day.

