### Data collection

The participants’ general characteristics, including sex, age, body mass index (BMI), heart rate (HR), blood pressure (BP), and electrocardiogram (ECG) data, will be collected. To assess the effect of VR immersion on stress among night-shift anesthesiologists, data will be collected from participants in the intervention group at six timepoints: baseline status (07:50 am, T1), initiation of night shift (17:30, T2), before first VR immersion (23:30, T3), after first VR immersion (23:50, T4) on the day that they work the night shift and before second VR immersion (07:30, T5), and after first VR immersion (07:50, T6) of the next day. At each timepoint, participants will be asked to measure their stress status via completing the scales which included NASA-TLX, CPSS, VAS, and MFI-20. In addition, ECG will be measured using a mobile ECG recorder (CardioLearn; HeartVoice Medical Technology Co., Ltd., Anhui, China) at each timepoint following the manufacturer’s instructions. The mobile device has been widely used in China to simply measure the ECGs and automatically analyze their results based on a novel deep learning-based cloud service as earlier reported [27, 28]. Furthermore, the anesthesiologists will be invited to record their ECG whenever they feel discomfort during the night shift. The incidence of arrhythmia, level of satisfaction, and incidence of chest distress, headache, or heart palpitations will also be recorded by the researchers. The data recording flow chart is presented in Fig. 2 and the SPIRIT figure is shown in Fig. 3.

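### Heart rate, blood pressure, satisfaction, arrhythmia and symptoms are compared by independent-sample tests although both crossover conditions contain the same people

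*Protocol article*

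**What the plan says.** Under Study design, the trial "is a randomized controlled, single-center clinical trial using a crossover design with a washout of 1 week". Participants are randomized to the order of the two conditions, and under Setting "each anesthesiologist only undergoes one night shift each arm and works from 17:30 to 8:00 of the next day". Everyone who completes the study therefore contributes to both conditions.

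Study design lists heart rate, blood pressure, satisfaction, arrhythmia and symptoms as secondary outcomes alongside CPSS, VAS and MFI-20. Analysis of the secondary outcomes treats the two sets differently:

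- CPSS, VAS and MFI-20 get an analysis of variance named for the 2×2 crossover.
- "The age, BMI, HR, MBP, and the level of satisfaction between groups will be analyzed by the Student" t test, with the Wilcoxon rank-sum test as alternative.
- Gender and the "incidence of arrhythmia, chest distress, headache, and heart palpitations between groups will be analyzed by the Pearson" χ² test or Fisher's exact test.
- Spearman's rank correlation is to "analyze the association between work hours and scores on the scales".

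Data analysis explains between-group, for quantitative data, as intervention group against control group.

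**The concern.** Rank-sum, Pearson χ² and Fisher's exact tests all assume two independent samples. The t test has the rank-sum test, not the signed-rank test, as its alternative, so it reads as the two-sample t test. Here the two samples are the same people on two nights. The tests as stated charge the treatment comparison with person-to-person variation that the crossover was chosen to remove, and they leave no place for a period effect.

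With 30 participants, within-person comparison is the main strength of the design. Giving it up for five kinds of declared secondary outcome makes non-significant results hard to interpret. It also leaves two sets of secondary outcomes, from the same people on the same nights, analysed on incompatible assumptions.

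Age, BMI and gender stand in the same between-group sentences. They cannot differ between two conditions made up of the same people, so those tests are empty.

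**Working it through.** The documents give no figure for these outcomes to reproduce: the sample size calculation concerns NASA-TLX only. The check is what an unpaired test does to paired data. Correlations between nights for heart rate, blood pressure and satisfaction are not given and are assumed.

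**1. Continuous outcomes, true size.** Let each night's value have variance σ² and let r be the correlation between a person's two nights.
- True variance of the difference in means: 2σ²(1 − r)/n.
- Variance that the unpaired t test uses: about 2σ²/n.
- Large-sample size at nominal 5%: 2Φ(−1.96/√(1 − r)).

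| Assumed r | Formula | Simulated, n = 30 |
|---|---|---|
| 0.3 | 2Φ(−2.34) = 1.9% | about 2% |
| 0.5 | 2Φ(−2.77) = 0.56% | about 0.7% |
| 0.7 | 2Φ(−3.58) = 0.03% | 0.06% to 0.08% |

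The paired t test keeps its 5% size throughout.

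**2. Is that range of r plausible?** The only guide is the NASA-TLX pilot under Sample size estimation: SDs 16.8 and 18.2, SD of the difference 12.1.
- 12.1 as worded: r = (16.8² + 18.2² − 12.1²)/(2 × 16.8 × 18.2) = 467.07/611.52 = 0.76.
- 12.1 as a within-subject SD, so that the variance of the difference is 2 × 12.1² = 292.82: r = (613.48 − 292.82)/611.52 = 0.52.

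These are before and after scores on another scale, not two nights, so they illustrate only.

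**3. Power, same illustration.** Take 26 people, the pilot difference 65.5 − 55.7 = 9.8, and 12.1 as worded. The unpaired t test has about 52% power and the paired test about 98%. At assumed r of 0.3 and 0.5 the unpaired test has about 51%, against 64% and 79% for the paired test.

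**4. Binary outcomes, an invented table.** Of 30 people, 8 have a symptom on both nights, 6 on the control night only and none on the VR night only. The margins are 14/30 and 8/30.
- Pearson χ² = 0.2²/[(22/60)(38/60)(2/30)] = 2.58, P = 0.108.
- Fisher's exact test, P = 0.180.
- Exact McNemar on the 6 discordant pairs, P = 2 × 0.5⁶ = 0.031.
- Mainland–Gart, if the 6 fall 3 and 3 across the sequences: Fisher on the 2×2 table of discordant pairs, P = 2/C(6,3) = 2/20 = 0.10.

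Pairing can change the answer. The last line shows that much of the gain from McNemar depends on taking period effects as negligible.

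**5. Why a rank-sum test can be used correctly.** Write the treatment effect as τ and the period effect as π. The period 1 minus period 2 difference has expectation π + τ in the VR-first sequence and π − τ in the other. Comparing these differences between sequences estimates 2τ, and π cancels. The sequences are independent groups of people, so two-sample tests are valid there. They are not valid on the raw values of the two conditions.

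**6. Work hours.** Each shift "works from 17:30 to 8:00 of the next day", so within the trial hours worked have little room to vary except by timepoint. Under Data collection, "At each timepoint, participants will be asked to measure their stress status via completing the scales". If timepoint stands for work hours, the Spearman test uses several scores from each person. On VR nights, every score from T4 onward also follows a VR session, which mixes time on shift with treatment.

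**The case against.** A condensed article may leave analysis detail to a fuller document. That does not help here, because the article names the tests and says what they compare; the point is a wrong statement, not a missing one.

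A better objection is that two-sample tests are not foreign to crossovers. As step 5 shows, they are standard when applied to period differences between sequences, and Mainland–Gart is itself a comparison between sequences. Data analysis also promises a further comparison of quantitative data that appears to mean sequences. This stands in part: the fault lies in the groups and values to which the tests are applied, not in the tests. But the text applies them between groups, and reading groups as sequences would make the tests on raw heart rate or symptoms say nothing about VR.

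It is also fair that the error is conservative in the simple case. A reader might infer inflated false positives, or harms being missed. With one record per person per night and positive correlation, false positives fall rather than rise. The documents give no event rates, and the invented table favours VR, so it says nothing about missed harm. Inflation would need several timepoints pooled as independent rows, which the article does not say will be done.

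The same caution applies to Spearman. A reader might infer that a dozen scores per person are pooled, with many false positives. Pooling is not stated, and "data will be collected from participants in the intervention group at six timepoints" fixes the schedule explicitly only for the VR condition. If 12 scores were pooled and hours varied only by timepoint, simulated type I error was 0.025 down to 0.0003 at assumed intraclass correlations of 0.3 to 0.76, below nominal.

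**Conclusion.** The tests stated for heart rate, mean blood pressure, satisfaction, arrhythmia, chest distress, headache and palpitations do not fit the crossover and should be changed. The consequence is P values that are too large and lost power, with a true size of about 2%, 0.7% and below 0.1% in place of 5% at assumed between-night correlations of 0.3, 0.5 and 0.7. This rests on one record per person per night, positive correlation and 30 people; with no correlation the size would be close to nominal.

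The point does not reach the primary outcome or the treatment comparisons of CPSS, VAS and MFI-20, which have an analysis named for the crossover. Testing age, BMI and gender between conditions is uninformative but does no inferential damage. The Spearman point is secondary and conditional on work hours being represented by timepoint.

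**What to change.** In Analysis of the secondary outcomes:

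- **Heart rate, mean blood pressure, satisfaction:** use a crossover model with treatment, period, sequence and participant. If the data are non-normal, use a rank-sum test comparing within-person period differences between the two sequences.
- **Arrhythmia, chest distress, headache, palpitations:** use the Mainland–Gart test, or exact McNemar if period effects are taken as negligible, and state that assumption.
- **Age, BMI, gender:** tabulate by sequence, without tests.
- **Work hours and scale scores:** define work hours, and replace the simple Spearman test with a method that allows for repeated scores per person and adjusts for condition.

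The cost is analysis wording only. Sequence and period are known from the randomization, and no extra data, visits or participants are needed. The change should be made before the analyst sees results by condition.

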## Discussion

This study will be the first to evaluate the potential effectiveness of VR technology in reducing stress among night-shift anesthesiologists. Work overload, long working hours, and continuous noise pollution [30, 31] are among the factors that cause physical and mental problems among anesthesiologists, such as psychological distress, burnout syndrome (BOS), and memory and attention problems [32, 33]. It has been reported that mental fatigue is the main cause of medical error among anesthesiologists [34] as well as the main reason for the high proportion of suicides among these doctors [35]. A study showed that the risk of medical accidents increases exponentially with each hour of work after the doctor has worked for 9 h consecutively. Moreover, the impairment of psychomotor function may be equivalent to a blood alcohol concentration of 0.1% if the doctor has experienced 24 h of sustained wakefulness; this concentration is higher than the legal limit for driving in most states in the USA [36]. It has also been reported that the rate of burnout among anesthesiologists is 48%, higher than that among all physicians among the specialties studied [37]. The burnout rate among Chinese anesthesiologists is 69%, while their consultation rates are 73% [38]. It is an urgent necessity to take more measures to curb psychological distress without increasing the number of anesthesiologists.

VR technology has been widely used in clinical practice to treat mental illnesses and reduce preoperative anxiety in both healthcare providers and patients [16, 17, 19]. Shah et al. [39] found that stress was the primary target and depression was the secondary target in the VR mood induction procedure study. The current study would provide evidence affirming the use of VR technology to reduce stress among night-shift anesthesiologists. These results might be attributed to the fact that watching VR videos could reduce the long hours of night-shift work, distract the anesthesiologists, and allow them to rest, thus making them positive and vibrant again.

However, there are still several limitations in the study. First, because of the connectivity issues of VR technology, a nonimmersive environment may arise, which may interfere with participant relaxation and the subsequent level of satisfaction. Second, in the current study, to better ensure the safety of patients, we will arrange another extra qualified anesthesiologist to take over the participants’ work during the VR immersion. However, this might be unlikely in the real-world where extra anesthesiologists are not always present. We hope the results of the study may spur managers to take measures to enable the anesthesiologists to enjoy VR entertainment during the night shift in the future. Third, the study is a single-center, crossover design with a small sample size. Therefore, it is better to confirm the preliminary results by conducting a large-scale multicenter study.

Although VR technology has been widely used in biomedical fields, it is still unknown whether the use of VR can reduce stress among night-shift anesthesiologists during working hours. A positive result in this trial could spur hospitals to apply the technology to reduce stress among night-shift doctors in every department, thus creating a relatively relaxed working environment that can benefit both doctors and patients.

## Data Availability

Data of this study are available on reasonable request from the corresponding authors. The data is monitored by the corresponding authors and scientific research department of the hospital.

## Abbreviations

ASA: American Society of Anesthesiologists
BOS: Burnout syndrome
BMI: Body mass index
CPSS: Chinese Perceived Stress Scales
CRH: Corticotropin-releasing hormone
CRP: C-reactive protein
ECG: Electrocardiogram
HR: Heart rate
IRB: Institutional Review Board
MBP: Mean blood pressure
MFI-20: Multidimensional Fatigue Inventory
NASA-TLX: NASA Task Load Index
PTSD: Posttraumatic stress disorder
VAS: Visual analogue scale
VR: Virtual reality
